#### Scenario Creation

From the same data set used to develop the CDS model, 20 patients were selected to constitute the target population in this study by using stratified random sampling. The stratification was made to ensure that there are equal amounts of readmitted patients and control patients. For each of these 20 patients, scenarios comprising narrative reports and clinical data describing demographics, and clinical events and outcomes, including potential readmittance, were recreated retrospectively based on real patient historical data from the regional database of electronic health data.

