### Experimentation and Data Collection

The experiment simulates the decision-making process of a patient’s discharge, further treatments, and care plan, based on real historical data. Patient data for model output are preloaded into the CDS model. The participants will be randomly paired with 1 physician and 1 nurse in each pair, reflecting the real-world setup in the decision-making regarding the patient’s potential readmission (Figure 1). Pairs will then be randomly assigned into test (n=3) and control (n=3) groups using simple randomization with stratification. The pairs in the test group will be given 10 scenario descriptions, patient electronic health record (EHR) data, and the CDS model output based on each of the 10 patients. The pairs in the control group will be given the same 10 scenario descriptions and EHR data but not the CDS model output. After making decisions based on the 10 scenario descriptions the test group and the control group will switch roles and 10 new scenario descriptions will be given to the groups, again with and without the CDS model output.

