**Figure 1 figure1:**
[figure not shown]
Flowchart for the randomized controlled cross-over design. CDS: clinical decision support; EHR: electronic health record.

Before the experiment, each group will be briefly trained in how the CDS model works and how to interpret its output [14,15]. The clinicians will be asked to think aloud so that both the conversation and reasoning during the decision process are recorded. The scenarios will be presented to the clinicians via a text document in a separate computer room at the hospital, and the CDS output in a web-based interface as depicted in Figure 2. The clinicians will be able to either make a decision or request for more information about the patient, which will be provided by an additional clinician who is part of the research group that will be in another room using a chat function on the local information system. This clinician is connected to the EHR system and has access to all patient data. The additional information can include admission notes, laboratory test results, and medication lists, and this procedure will be carefully explained to the clinicians before the experiment. This information will not be available from the beginning, to mimic the real-world information search between different systems or system modules and to research what level of information would be sufficient to decide in both groups; a clinician shall provide extra information about the patient only if requested. Every such request will be documented by the researchers present in the rooms together with the clinicians, observing the decision-making and the experiment. All clinical notes available in the experiment will undergo a deidentification process before this study. The decisions made by the participants will be noted by the observing researcher.

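### As worded, the scenarios include the patient's later outcome and no time cut-off is stated for participant materials or chat replies, although decisions are compared with what followed

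*Protocol article*

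**What the plan says.** Scenario Creation describes 20 cases drawn from the data set used to develop the model, half of them readmitted. It lists what each scenario comprises: narrative reports and "clinical data describing demographics, and clinical events and outcomes, including potential readmittance, were recreated retrospectively based on real patient historical data".

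Experimentation and Data Collection says what the pairs receive:

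- With the decision support output: "The pairs in the test group will be given 10 scenario descriptions", together with health record data and the model output.
- Without it: "The pairs in the control group will be given the same 10 scenario descriptions and EHR data but not the CDS model output".
- Form of delivery: "The scenarios will be presented to the clinicians via a text document in a separate computer room at the hospital".

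The same section allows a pair to ask for more information by chat. The request goes to a clinician from the research group who sits in another room:

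- Access: "This clinician is connected to the EHR system and has access to all patient data".
- Examples of what may be released: "The additional information can include admission notes, laboratory test results, and medication lists".
- Condition for release: "a clinician shall provide extra information about the patient only if requested".
- Processing of the notes: "All clinical notes available in the experiment will undergo a deidentification process before this study".

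Table 1, in the row on decision quality, compares the test group's decisions with the decision actually made for the patient and the event that came after it, and with the control group's decisions on the same patients.

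**The concern.** The experiment simulates a discharge decision. That works only if participants know what was knowable at that moment. The tool's product is a 30-day readmission risk with an explanation. Where the readmission itself is already visible, the tool has nothing left to add on that point, and the comparison with later events no longer measures what the tool contributes.

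The text leaves two routes open: the scenario document, and a chat reply drawn from a record that may run past the index stay. Decision quality would be affected most directly. Agreement with the model, speed and confidence could also shift if a pair knew the outcome. With six pairs and a mainly descriptive analysis, it would be hard to separate such an effect afterwards.

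**Working it through.** The protocol gives no figure on this point, so there is nothing to reproduce. The check sets the statements side by side.

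1. **Scenario content.** Scenario Creation names outcomes, including potential readmittance, among the things the scenarios comprise.
2. **Who sees the scenarios.** Experimentation and Data Collection uses the same word for what the clinicians are shown as a text document. No section distinguishes a participant version from a researcher version.
3. **Chat route.** The responder has access to all patient data. The items named are introduced as examples, and a request is the only stated condition for release. No time limit is given. The cases are historical (admissions from 2017 to 2019, under CDS Model), so a complete record could include entries made after the index discharge.
4. **Processing.** De-identification is the only processing of notes that is described. It removes identity, not later events.
5. **Comparator.** Table 1 uses the subsequent event as one reference for decision quality.

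Taken literally, steps 1 and 2 place the comparator of step 5 in participants' hands. Steps 3 and 4 do not close the second route.

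**Direction of the effect, with assumed inputs.** Let p1 and p0 be the proportions of decisions in line with the later event, with and without the output, when nothing is disclosed. Suppose that disclosure makes every affected decision match.

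- *Equal disclosure, share L in both conditions.* The difference is [L + (1 - L)p1] - [L + (1 - L)p0] = (1 - L)(p1 - p0). The factor is 1 at L = 0, 0.5 at L = 0.5 and 0 at L = 1. This fits the scenario-text route, because under Methods both conditions read the same descriptions.
- *Unequal disclosure, L1 with and L0 without the output.* The difference is (p1 - p0) + L1(1 - p1) - L0(1 - p0), which can fall on either side of p1 - p0. This fits the chat route, where the pairs' requests and the responder's answers may differ by condition.

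The documents give none of L, L1, L0, p1 or p0. The values of L above span the possible range and are not estimates.

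**The case against.** The strongest reply is that Scenario Creation describes how the cases were rebuilt, not what is handed over, and that the outcome was rebuilt so that the Table 1 comparison could be made. A simulated discharge decision makes little sense if the pair is told whether the patient came back. That is probably what the authors meant. It does not remove the point, because the article never says it and uses one term for both things.

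On the chat, the named examples are ordinary inputs to a discharge decision. The procedure is explained to participants beforehand, every request is documented, and the study process is to be tested before data collection. These safeguards count: a request for later events would be on record. They would not reveal an outcome already in the scenario text, and they set no limit on the reply.

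Several stronger readings are tempting and are not supported:

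- *The responder may release anything.* The text gives access to all data and release on request. It states no limit, which is not the same as permission.
- *The responder is unmasked.* The article is silent, and an article commonly leaves such detail to the full protocol. Taken alone this would be no finding. It matters here only because the responder controls what information reaches the pairs.
- *Participants will recognise patients.* This is speculative, given admissions from 2017 to 2019, an experiment from October 2023 and de-identified notes.
- *Participants are scored against the outcome.* Decision quality is an exploratory, descriptive comparison with several references, and the listed decisions do not map directly onto readmitted or not.

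**Conclusion.** The concern holds as a defect of wording and stated procedure. Read literally, the article puts the later outcome in the scenarios, gives the scenarios to participants, sets no time limit on chat replies and compares decisions with that outcome. It is not proof that leakage will occur.

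The size cannot be estimated from the documents. Equal disclosure in both conditions would shrink the contrast, on the assumption that clinicians who know the outcome decide in line with it. Unequal disclosure could move the contrast either way. This should be fixed before data collection, because a disclosed outcome cannot be withdrawn afterwards.

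**What to change.** 1. Reword Scenario Creation so that participant scenarios contain only entries dated before the index discharge decision. State the same limit for chat replies in Experimentation and Data Collection.
2. Keep the decision actually taken and all later events in a separate file for the analysts.
3. Give the chat responder only a look-up pack cut at the same time point, and do not tell them whether the pair has the decision support output. The responder already works from another room by chat.

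The scenarios are described as already recreated, so the work is to check and split existing files and to prepare the look-up packs before the experiment. It needs no change to the number of participants or scenarios, or to the crossover design. If the outcome is already withheld in practice, a sentence saying so, with the cut-off, settles most of the point.

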### Recruitment

The participants involved in the experimentation will include both physicians (n=6) and nurses (n=6) and will be recruited from the clinical staff at the 2 hospitals based on the following inclusion criteria: a minimum of 3 years of experience in the treatment of patients with HF, and currently active engagement in clinical practice within either of the 2 specialized cardiology departments in the region. This study will use purposeful sampling [9] for recruiting physicians and nurses according to the inclusion criteria, a process led by the hospital. Although there might be a limited availability of staff, physicians and nurses who were involved in the design of this study and the CDS model will be excluded from participation in this study, to prevent bias.

### Experimentation and Data Collection

The experiment simulates the decision-making process of a patient’s discharge, further treatments, and care plan, based on real historical data. Patient data for model output are preloaded into the CDS model. The participants will be randomly paired with 1 physician and 1 nurse in each pair, reflecting the real-world setup in the decision-making regarding the patient’s potential readmission (Figure 1). Pairs will then be randomly assigned into test (n=3) and control (n=3) groups using simple randomization with stratification. The pairs in the test group will be given 10 scenario descriptions, patient electronic health record (EHR) data, and the CDS model output based on each of the 10 patients. The pairs in the control group will be given the same 10 scenario descriptions and EHR data but not the CDS model output. After making decisions based on the 10 scenario descriptions the test group and the control group will switch roles and 10 new scenario descriptions will be given to the groups, again with and without the CDS model output.

**Figure 1 figure1:**
[figure not shown]
Flowchart for the randomized controlled cross-over design. CDS: clinical decision support; EHR: electronic health record.

Before the experiment, each group will be briefly trained in how the CDS model works and how to interpret its output [14,15]. The clinicians will be asked to think aloud so that both the conversation and reasoning during the decision process are recorded. The scenarios will be presented to the clinicians via a text document in a separate computer room at the hospital, and the CDS output in a web-based interface as depicted in Figure 2. The clinicians will be able to either make a decision or request for more information about the patient, which will be provided by an additional clinician who is part of the research group that will be in another room using a chat function on the local information system. This clinician is connected to the EHR system and has access to all patient data. The additional information can include admission notes, laboratory test results, and medication lists, and this procedure will be carefully explained to the clinicians before the experiment. This information will not be available from the beginning, to mimic the real-world information search between different systems or system modules and to research what level of information would be sufficient to decide in both groups; a clinician shall provide extra information about the patient only if requested. Every such request will be documented by the researchers present in the rooms together with the clinicians, observing the decision-making and the experiment. All clinical notes available in the experiment will undergo a deidentification process before this study. The decisions made by the participants will be noted by the observing researcher.

**Figure 2 figure2:**
[figure not shown]
CDS model output showing readmission risk and explanations of model decision for a hypothetical patient. AI: artificial intelligence; CDS: clinical decision support; CDSS: clinical decision support system; HF: heart failure.

At the end of the experiment, each clinician will be interviewed individually by the researcher using the interview questions defined in Multimedia Appendix 1. The dialogue will be audio-recorded and transcribed verbatim.

### Outcome Measures

A research-based evaluation framework specifically designed for AI-based decision-support systems [16] has guided and inspired the selection of the outcome measures for this study. The added value of the AI system will be assessed through a mixed methods evaluation design: process efficiency and patient-related outcomes shall be assessed using a quantitative approach, while quality, reliability, trust, and similar parameters shall be addressed through qualitative semistructured interviews. Table 1 provides details on the outcome measures selected for this study.

**Table 1 table1:** Outcome measures.

Outcome indicator		Goal	Analytic approach
**Impact on decision-making**			
	Decision consistency	To explore decision consistency between the users and the CDS^a^ model to research whether having the CDS model increases uniformity among the decisions taken compared to decisions without the model.	Comparing the taken decisions: Between the CDS model output and the test group to assess the extent of how much the users agreed with the model output. Between test and control groups to assess similarity in decisions taken with and without the model output. Potential decisions: To discharge, with x, y, and z treatment. Move to another department (which?). Take additional tests for an extended investigation. To send a referral or follow-up at outpatient clinical, primary care, or home care. To stay for some more days.
	Decision quality	To explore whether the CDS model could improve decisions.	Comparing decisions taken by the test group with: Historical data—what decision was actually taken for the patient and what event followed afterwards. Control group’s decisions on the same patients to control the influence of the experiment and set up over the decisions taken: do decisions differ from the test group and the historical data?
	Work efficiency	To explore performance changes due to using the CDS model output.	Measuring speed of decision-making for both test and control groups. Comparing the average speed between groups with and without CDS.

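### The decision consistency row asks whether CDS makes decisions more uniform, but neither listed comparison measures uniformity within a condition or gives an unaided baseline

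*Protocol article*

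**What the plan says.** All of this is in the protocol article. In Table 1, the goal of the decision consistency row has two parts: to explore consistency between users and the model, and "to research whether having the CDS model increases uniformity among the decisions taken compared to decisions without the model". The analytic approach in the same row names two comparisons:

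- The first concerns only the pairs who see the output, and asks how often their decisions match it.
- The second sets the two conditions against each other: "Between test and control groups to assess similarity in decisions taken with and without the model output".

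The row then lists five kinds of possible decision, some of which can be combined.

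Under Experimentation and Data Collection, there are three physician-nurse pairs per group: "Pairs will then be randomly assigned into test (n=3) and control (n=3) groups using simple randomization with stratification". Both groups decide on the same patients: "The pairs in the control group will be given the same 10 scenario descriptions and EHR data but not the CDS model output". Then "the test group and the control group will switch roles and 10 new scenario descriptions will be given to the groups". The caption of Figure 2 describes what a pair with CDS sees: "CDS model output showing readmission risk and explanations of model decision for a hypothetical patient".

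The Data Analysis section says only that the quantitative work is mainly descriptive and names no agreement index. The decision quality row compares the test group with the historical course and with the control group, so it does not supply a measure of uniformity either.

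**The concern.** Uniformity with CDS compared with uniformity without it is one quantity measured twice: how far pairs agree with one another when they have the output, and how far they agree when they do not. The row lists neither measurement. The test-control comparison crosses the two conditions, so it reflects whether CDS changes decisions. The test-model comparison is made in one condition only.

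Decision consistency is the first of the key outcomes named in the Abstract and bears directly on the study's primary aim. If the row is followed as written, the report could state how similar aided and unaided decisions were, and how often aided pairs followed the model. It could not state whether the tool made decisions more uniform. Agreement with the model would also stand without the figure needed to judge how much of it would have occurred anyway.

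**Working it through.** The plan gives no figure for this outcome, so there is nothing to reproduce. The check is whether the listed comparisons identify the stated goal.

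**Inputs from the article.** Three pairs per condition, the same scenarios in both conditions, 20 scenarios in all.

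**Assumed inputs.** The decision probabilities below are illustrations. Pairs are taken to decide independently within a scenario.

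**Definitions for one scenario.** Let p be the distribution of decisions with CDS and q the distribution without.

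- Agreement between two pairs with CDS: Σp². Without CDS: Σq².
- Goal (uniformity with versus without): Σp² − Σq².
- Test-control similarity: Σpq.

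**1. Five options.** Take q = (0.40, 0.10, 0.15, 0.20, 0.15).

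Σq² = 0.16 + 0.01 + 0.0225 + 0.04 + 0.0225 = 0.255.

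| Decisions with CDS, p | Σp² | Σp² − Σq² | Σpq |
|---|---|---|---|
| Same as q | 0.255 | 0 | 0.255 |
| (0.80, 0.05, 0.05, 0.05, 0.05) | 0.650 | +0.395 | 0.350 |
| (0.05, 0.05, 0.05, 0.80, 0.05) | 0.650 | +0.395 | 0.200 |
| (0.20, 0.20, 0.20, 0.20, 0.20) | 0.200 | −0.055 | 0.200 |

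For the third row, Σpq = 0.05 × (0.40 + 0.10 + 0.15 + 0.15) + 0.80 × 0.20 = 0.04 + 0.16 = 0.20. The last two rows have the same similarity, but uniformity rises in one and falls in the other. The second and third rows have the same uniformity but different similarity.

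**2. Two options.** Let a pair choose the first option with probability p₁ with CDS and q₁ without. Then Σpq = p₁q₁ + (1 − p₁)(1 − q₁) and Σp² = p₁² + (1 − p₁)².

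| p₁ | Σp² | Σpq if q₁ = 0.5 | Σpq if q₁ = 0.7 |
|---|---|---|---|
| 0.5 | 0.50 | 0.50 | 0.50 |
| 0.7 | 0.58 | 0.50 | 0.58 |
| 0.9 | 0.82 | 0.50 | 0.66 |
| 1.0 | 1.00 | 0.50 | 0.70 |

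With q₁ = 0.5 similarity is blind to uniformity. With q₁ = 0.7 it moves with uniformity over this range. It still does not identify it: with q₁ = 0.8, p₁ = 1 and p₁ = 0 both give perfect uniformity (Σp² = 1.00), but similarity is 0.80 in one case and 0.20 in the other.

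**3. Agreement with the model.** Suppose test-group agreement is 70%. The with-minus-without difference depends on a figure the row does not ask for:

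| Unaided agreement | Difference |
|---|---|
| 50% | +20 points |
| 60% | +10 points |
| 70% | 0 |
| 80% | −10 points |

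**4. What the planned data allow.** Three pairs give 3 × 2 / 2 = 3 pair-to-pair comparisons per scenario and condition, so 3 × 20 = 60 with CDS and 60 without. For agreement with the model there are 3 × 20 = 60 pair-decisions in each condition. These come from six pairs and are correlated. Within one scenario, agreement among three pairs can only be 3/3, 1/3 or 0/3.

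**The case against.** The strongest reply is that the test-control line is loosely worded. It could mean comparing, between the groups, how similar decisions are with the output and how similar they are without it. The goal in the same row favours that intention. If so, the within-condition contrast is planned and only poorly expressed. This lowers confidence about intent, but the line as written speaks of similarity between the groups and names no within-group measure. It also leaves the missing unaided agreement with the model untouched.

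A second reply is that a condensed article may leave the choice of agreement index to a fuller plan. That is fair for the index and its formula. It does not cover this point, because the table itself fixes which comparisons serve the goal, and they do not match it.

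Three stronger conclusions are tempting and are not supported:

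- A reader might infer that test-control similarity carries no information on uniformity. That holds only in special cases such as an even unaided split between two options; with an unaided probability of 0.7 it does vary.
- A reader might infer that the row answers none of its goal, or that the authors will read test-model agreement as the effect of CDS. The table gives that comparison a narrower, descriptive purpose, which it serves validly.
- A reader might infer that the study cannot go ahead without the change. The outcome is worded as exploratory, no test or sample size rests on it, and decisions are recorded in both conditions.

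**Conclusion.** The point holds in a limited form. On the plain reading of Table 1, the two comparisons do not measure the uniformity part of the decision consistency goal, and agreement with the model lacks an unaided reference. In the illustrations the listed similarity is 0.20 whether uniformity rises by 0.395 or falls by 0.055, and an observed 70% agreement with the model is compatible with effects of either sign. These sizes rest on assumed probabilities and on independent decisions within a scenario; the conclusion that similarity does not in general identify uniformity does not depend on the particular values.

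It should be fixed before analysis. It is not critical, because the outcome is exploratory and descriptive and nothing is lost from the data collection. The remedy also depends on both groups deciding on the same patients, as the Methods state; the Abstract instead gives the control group different scenarios.

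**What to change.** Keep both listed comparisons, labelled for what they show: how far aided decisions differ from unaided ones, and how far aided pairs agreed with the output. Add to the decision consistency row:

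1. For each scenario, the share of agreeing pair-to-pair comparisons among the three pairs with CDS and, separately, among the three without. Report the with-minus-without difference over the 20 scenarios.
2. Agreement with the model for the unaided pairs too, with the with-minus-without difference.

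State before the experiment what counts as agreement when a decision has several components, and how the readmission risk output is mapped to the listed kinds of decision. The existing test-model comparison already needs this mapping. Present the 60 comparisons per condition as correlated descriptive data from six pairs, not as independent observations. Reconcile the Abstract with Experimentation and Data Collection on whether the groups receive the same ten scenarios in each half; a like-for-like comparison needs the same ones.

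The cost is some added text in Table 1 and the analysis description, plus the work of agreeing the two definitions. No new data are needed.

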In this project, our objective is to evaluate the applicability and potential benefits of a previously established ML model for predicting unscheduled readmission of patients with HF within 30 days after discharge from medical care [5]. This model has been further fine-tuned and tailored for practical integration and usage within clinical settings [3,7], encompassing the identification of potential barriers and enablers for implementing a clinical decision support (CDS) tool presenting the model output for clinical use. Refinement also encompassed the augmentation of the model with interpretability features and a comprehensive exploration of the optimal timing and manner in which the model’s findings should be presented to users within the clinical domain [7]. The primary aim of the study outlined in this protocol is to investigate how the developed CDS tool alters the decision-making processes of health care professionals in the specific context of discharging patients with HF, and if so, in which ways. Additionally, the aim is to capture the experiences of health care practitioners as they engage with the system’s outputs to analyze usability aspects and obtain insights related to future implementation.

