### Data Analysis

The quantitative analysis will primarily employ descriptive statistics. The interview data to address the rest of the outcome measures shall be transcribed and thematically analyzed using the thematic coding scheme corresponding but not limited to the outcome measures of this study (Table 1) [16-18].

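### Table 1 compares decisions with and without the CDS on the same patients, but different clinician pairs make them and no within-condition disagreement is reported, so a difference cannot by itself be attributed to the CDS

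*Protocol article*

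**What the plan says.** The primary aim in the Introduction of the protocol article is "to investigate how the developed CDS tool alters the decision-making processes of health care professionals". Table 1, under impact on decision-making, lists the comparisons that bear on it:

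- **Decision consistency.** The goal is to learn "whether having the CDS model increases uniformity among the decisions taken compared to decisions without the model". The listed comparisons are "Between the CDS model output and the test group to assess the extent of how much the users agreed with the model output" and "Between test and control groups to assess similarity in decisions taken with and without the model output".
- **Decision quality.** Test decisions are compared with the historical record and with control decisions on the same patients. The control comparison is meant to account for the influence of the experimental set-up, and it asks "do decisions differ from the test group and the historical data".

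Experimentation and Data Collection gives the design: "Pairs will then be randomly assigned into test (n=3) and control (n=3) groups using simple randomization with stratification". Both groups receive the same 10 scenarios, one with and one without the CDS output. They then switch roles on 10 new scenarios. Data Analysis adds: "The quantitative analysis will primarily employ descriptive statistics".

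**The concern.** A same-patient comparison of test with control looks like a clean contrast, since the patient is held constant. The deciders are not. For any one patient, the decisions with the CDS come from three pairs and the decisions without it from three others. The crossover does not help here: each pair works under both conditions, but on different patients.

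The Introduction itself describes discharge assessment as partly subjective and uncertain, so some disagreement between pairs must be expected whatever the tool does. A reader of the results needs to know how much of the test-control disagreement exceeds what two pairs under the same condition would show. None of the comparisons listed in Table 1 supplies that. At stake is the interpretation of the main quantitative result on decisions: the same disagreement figure could reflect a real shift or clinician variation alone.

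**Working it through.** **Inputs from the document.** 20 scenarios; 6 pairs, 3 with and 3 without the CDS on each scenario; five listed types of decision. The Abstract can be read as giving the control group other scenarios. I follow Experimentation and Data Collection, which agrees with Table 1 that the patients are the same. The document states no agreement rate, sample-size calculation or test, so there is no figure of its own to reproduce.

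**Assumptions.** Pairs decide independently. On each scenario one action has probability p and the other four share the rest equally. Agreement between two pairs is then A = p² + (1−p)²/4. A is varied from 0.6 to 0.9.

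**Step 1: no CDS effect.** All six pairs draw from the same distribution, so any two of them disagree with probability 1 − A, whether or not they are in the same condition.

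| Assumed agreement A | Cross-condition disagreement | Within-condition disagreement | Excess |
|---|---|---|---|
| 0.6 | 40% | 40% | 0 |
| 0.7 | 30% | 30% | 0 |
| 0.8 | 20% | 20% | 0 |
| 0.9 | 10% | 10% | 0 |

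Simulation of the 20-scenario, six-pair design gives the same values.

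**Step 2: a real effect and no effect can give the same raw figure.** Take A = 0.7 (p = 0.8325). Suppose the CDS moves 30% of test decisions on a scenario to one common action, which may be any of the five with equal chance (average probability 0.2).

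- Cross-condition agreement: 0.7 × 0.7 + 0.3 × 0.2 = 0.55, so disagreement is 45%.
- Agreement within the CDS condition: 0.7² × 0.7 + 2 × 0.7 × 0.3 × 0.2 + 0.3² = 0.343 + 0.084 + 0.09 = 0.517.
- Agreement within the control condition: 0.7.
- Mean within-condition disagreement: 1 − (0.517 + 0.7)/2 = 0.3915.
- Excess: 0.45 − 0.3915 = 0.0585, about 6 points.

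With no CDS effect and A = 0.55, cross-condition disagreement is also 45%, but within-condition disagreement is 45% too and the excess is 0. The raw 45% does not separate the two cases; the excess does, on average.

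**Step 3: how noisy the excess is.** With no effect, its central 95% range over simulated studies is about −2.5 to +3.3 points at p = 0.9 and −4.7 to +5.8 points at p = 0.8. The example in step 2 (p = 0.8325) lies between these settings, so its average excess of about 6 points is near the upper edge of chance. With no effect, the excess is above zero in about 45%, 44%, 41% and 22% of studies at A = 0.6, 0.7, 0.8 and 0.9. A positive sign alone therefore shows nothing.

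**Step 4: what re-randomization can show.** Six pairs split 3:3 in 20 ways. The excess does not change when the two groups are swapped, which leaves 20/2 = 10 distinct splits and a smallest possible p of 1/10 = 0.10.

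**The case against.** The strongest reply is that the protocol never says a difference proves an effect. Its goals are exploratory, its analysis mainly descriptive, and the question about differing decisions sits in the decision-quality row as a check on the experimental set-up. That stands. A reader might infer that the study would almost certainly report a CDS effect even if clinicians ignored the tool. With no effect and a binary decision, at least one of 20 scenarios does show a test-control mismatch with probability 95.6% at 5% pairwise disagreement, and above 99% at 10%. But that becomes a false claim only under a rule that one mismatch is enough, and no such rule exists. If each group were first reduced to its majority decision, the probability would be 28% at 10% disagreement and 76% at 20%.

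A second reply is that similarity could mean comparing distributions, for example the share discharged in each condition. With randomized pairs, such a signed contrast is centred on zero when there is no effect. That also stands: the problem belongs to the scenario-by-scenario reading. The same-patient wording in the decision-quality row invites that reading.

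Third, think-aloud recordings, ratings of how far the CDS helped, and interviews also bear on how decision-making changes. They do, but they do not supply the missing reference for the quantitative comparison. Nor do the historical decisions, which were made by other clinicians.

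Finally, the uniformity goal implies within-condition agreement, and an article may leave the choice of statistic to a fuller plan. The goal does imply it. Yet the comparisons Table 1 lists under that goal do not include it, and nothing ties it to the test-control comparison.

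**Conclusion.** The point holds in a limited form. Because different pairs decide each patient under the two conditions, and no listed comparison measures disagreement within a condition, a scenario-level test-control difference cannot by itself be attributed to the CDS. Under the assumed agreement of 0.6 to 0.9, disagreement of 40% to 10% is expected with no effect. The true figure depends on an agreement rate the document does not give, and on treating pairs as independent; stable habits of individual pairs would change the chance ranges.

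It would go too far to conclude that the primary aim cannot be answered. That aim concerns decision processes, and the qualitative material addresses it directly. What is limited is the weight the quantitative decision comparison can carry.

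**What to change.** In Table 1, replace the unreferenced test-control comparison with the following, using a coding of decisions fixed beforehand:

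1. For each scenario, report the share of the 9 cross-condition pair comparisons (3 × 3) that disagree, beside the share of the 6 within-condition comparisons that disagree. Show the 3 with CDS and the 3 without separately as well; this serves the stated uniformity goal.
2. Average the difference between the two shares over the 20 scenarios and report it as the excess.
3. Show the excess against its values under the other 3:3 splits of the six pairs (10 distinct splits, smallest p 0.10). If the stratified randomization ruled out some splits, use only those that were possible; the smallest p is then larger.
4. State in Data Analysis that a merely positive excess is not read as a CDS effect and that the conclusion stays descriptive.

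The cost is a change of wording in Table 1 and Data Analysis and a few lines of code. The decisions are already to be recorded, so no participants or sessions are added. The downside is that the reported CDS influence will be smaller and less certain than the raw difference.
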